### Procedure for unblinding if needed {17b}

Due to the study characteristics, both the study participants and the research physiotherapist will be aware of the allocation groups. Consequently, no non-blinding procedure is planned.

## Data collection and management

### Plans for assessment and collection of outcomes {18a}

The data collection will take place through interviews, physical examinations, and medical record analyses. All data will be collected by experienced physiotherapists. The interviews will consist of semi-structured questionnaires produced by the researchers, in addition to questionnaires validated for the Brazilian population. Regarding the physical examination, the volume of the upper limb with lymphedema will be evaluated using perimetry, tissue characteristics using thermography, and muscle strength will be evaluated using dynamometry. These assessment resources will be used for all participants included in the study and performed before and after the initial 30 days of treatment and during follow-up (6 and 12 months). Data regarding oncological treatment and lymphedema treatment history will be obtained from physical and electronic medical records.

### Plans to promote participant retention and complete follow-up {18b}

Study participants will receive the necessary information to understand the evaluation flow and the importance of completing the follow-up, comprising a teleconsultation within 7 days after study inclusion (at the beginning of the treatment) and face-to-face returns for reassessment in 30 days, 6 months, and 1 year. Any study participant can withdraw and leave the study at any time without necessarily explaining the reasons for withdrawal. Thus, whenever problems contacting the participant by phone (call or text message) arise, the institution will ask the institution to send a telegram to the participant’s registered address, instructing them to contact the physiotherapy sector to schedule their appointment.

### Data management {19}

Data will be collected by two physiotherapists who will fill in the information on paper sheets. These will be stored in a safe place for a period of up to 5 years in case there is a need for revision or request by the ethics and research committee. The responsibility for filling in the data in the electronic spreadsheet will be for the same initial collectors who will manually fill. A third member of the study group will review all the data in the electronic database, checking with the paper forms, before exporting to Statistical Package for the Social Science (SPSS).

### Confidentiality {27}

All patients received a random identification number to guaranteeing anonymity. The information collected on paper forms will be stored in a safe place at the Institution’s Clinical Research Division for a period of up to 5 years, in case there is a need for review or request by the ethics and research committee. The data stored in an electronic spreadsheet will be under the responsibility of the main author.

### Plans for collection, laboratory evaluation, and storage of biological specimens for genetic or molecular analysis in this trial/future use {33}

Not applicable, as no biological material will be collected during this study.

## Statistical methods

### Statistical methods for primary and secondary outcomes {20a}

A descriptive analysis of the sociodemographic and clinical characteristics of the study population will be carried out through the distribution of absolute and relative frequencies for categorical variables and central tendency and dispersion measures for continuous variables. The thermographic analysis will be obtained by the average difference in temperatures of one limb in relation to the other and a cut-off point will be established. Data normality will be calculated using the Kolmogorov–Smirnov test. Group comparisons will be done by using Student’s *t* test or Wilcoxon test for continuous variables and chi-square test for categorical variables. The effect size of the mean outcomes will be calculated using Glass’s delta (considering 0.2 as small, 0.5 as medium, and 0.8 as large effects) [23]. Associations between the variables of interest and the outcome will be performed using univariate linear regression. Variables presenting *p* ≤ 0.20 will be included in the multiple linear regression model employing the stepwise forward method, and those with *p* < 0.05 or with clinical relevance will be maintained in the adjusted model. A significance level of 5% will be accepted, at a confidence interval of 95%. Statistical tests will be performed using the SPSS version 23.0 software.

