### Secondary outcomes

#### Lymphedema tissue features

These will be determined by means of thermography, a safe, non-invasive imaging method that determines the distribution of body surface temperatures according to physiological and pathological tissue conditions. Inflammation, metabolic subcutaneous tissue changes, and blood supply changes result in temperature gradient changes in the affected area. Thus, different lymphedema stages will be associated to different temperature distribution patterns. A Onepro LT Flir thermographic camera (4800 pixels), with a temperature capture range from – 20 °C to 120 °C will be used to this end. The study participants will be instructed to remain in a standing position, without garments or other trunk and upper limb accessories. Body surface temperatures will be recorded using a thermal camera in the orthostatic position, from the anterior and posterior limb portions, at a 2 m distance. The thermometric images will then be analyzed using the FLIR One***®*** software.

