### Sample size {14}

Considering the benefits of complex physical therapy when there is a percentage reduction in excess limb volume of 22% to 73% [21], and, for the use of compressive therapy, an estimated response of 33.5% reduction in excess limb volume [22], we stipulated a 35% variation in treatment response between the groups, with an estimated treatment response of 45% in the control group (standard care) and 80% in the intervention group. The sample size was calculated considering a confidence level of 95% with a study power of 80% and a 1:1:1:1 ratio between the intervention groups. Thus, a total population of 120 patients (30 in each group) will be required. To cover possible losses to follow-up and treatment interruption, a total of 20% will be added to the number of participants Therefore, the total sample to be included in this study will be of 144 women (36 in each group).

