### Strong points

This is the first study to comparatively evaluate the use of a self-adjusting compression garment versus traditional therapeutic compression resources applied to lymphedema treatments in two treatment phases, namely volume reduction and maintenance in the Brazilian population. Furthermore, this study is a pioneer in the use of clinical thermography to assess lymphedema tissue characteristics in affected upper limbs. Finally, the planned follow-up will allow for the observation of both short- and long-term outcomes.

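### The plan announces an undefined cut-off for the continuous thermography outcome and does not say whether the cut-off or the continuous value carries the arm comparison

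*Protocol article*

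**What the plan says.** The Outcomes section lists tissue features among the secondary outcomes and gives them one instrument: "These will be determined by means of thermography, a safe, non-invasive imaging method". It expects that "different lymphedema stages will be associated to different temperature distribution patterns", which ties the temperature readings to stage of disease and not to treatment arm.

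The analysis is one sentence in Statistical methods for primary and secondary outcomes {20a}. It takes the "average difference in temperatures of one limb in relation to the other and a cut-off point will be established". The article states no threshold, cites no source for one, and gives no rule for finding one.

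The same section then sends group comparisons to Student's t test or the "Wilcoxon test for continuous variables and chi-square test for categorical variables". A between-limb difference could enter through the first route, and the same difference cut in two could enter through the second. The article does not say which applies.

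Under Strong points, the article says that "this study is a pioneer in the use of clinical thermography to assess lymphedema tissue characteristics".

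**The concern.** The measure is continuous, and the plan commits to a cut-off that did not yet exist when the article was written. The verb is that a cut-off will be established, not applied. No reference is attached, although the same section cites a source for its effect-size benchmarks. The claim to be a pioneer also points away from an accepted threshold. The natural inference is that the cut-off will come from the trial's own women, about 30 evaluable per arm in each phase.

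Three things could then go wrong, depending on use:

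- **Power.** Comparing proportions above a threshold discards information that the continuous difference holds.
- **False positives.** If the threshold is chosen because it separates the arms, the chi-square test no longer has its nominal error rate.
- **Optimism.** If the threshold is chosen to discriminate stage or response and its sensitivity and specificity are read off the same data, they will look better than they are.

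Thermography is the only tissue outcome and is presented as a strength. A chance arm difference or an over-optimistic threshold could therefore be reported as a finding of the trial.

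**Working it through.** **Inputs from the article**
- 30 evaluable women per group, 36 enrolled (Sample size {14}).
- 5% level: "A significance level of 5% will be accepted, at a confidence interval of 95"%. Sidedness is not stated; two-sided is assumed.
- 80% power: "The sample size was calculated considering a confidence level of 95% with a study power of 80"%.
- No SD, expected difference or cut-off for thermography.

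**The plan's own figure.** The article has no figure for thermography to reproduce. As a check on the arm size, the primary-outcome calculation assumes a response gap "with an estimated treatment response of 45% in the control group (standard care) and 80% in the intervention group". With the pooled two-sided formula and mean proportion 0.625:

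n = [1.960·√(2·0.625·0.375) + 0.842·√(0.45·0.55 + 0.80·0.20)]² / 0.35² = (1.342 + 0.537)² / 0.1225 ≈ 28.8, so 29.

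The planned 30 gives 81.6% power. The arm size is sound for its purpose, but thermography played no part in it.

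**Assumptions for the check.** Normal data, equal SDs, two independent arms, uncorrected chi-square test at 5%. The standardised difference d is set so that a t test has about 80% power at 30 per arm:

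d = (1.960 + 0.842)·√(2/30) = 0.723 by the normal approximation, or 0.74 when the t distribution is allowed for.

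**1. Power lost by dichotomising, 30 per arm**

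| Analysis | d = 0.74 | d = 0.723 |
|---|---|---|
| t test on the continuous difference | 80% | 79% |
| Split at the pooled median | 68% | 66% |
| Cut fixed midway between the arm means | – | 61% |
| Cut chosen on a label unrelated to arm | – | 54% |

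At 36 per arm and d = 0.723 the four figures are 86%, 62%, 67% and 61%. The large-sample efficiency of a median split for normal data is 2/π = 0.64, so 30 women per arm carry about the information of 30 × 0.64 ≈ 19.

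The median-split power at 30 per arm is somewhat flattered. With so few possible tables, the test's actual size there is 6.9%; at 36 per arm it is 3.4%.

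**2. Type I error with no true difference**

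| How the cut-off is chosen | 30 per arm | 36 per arm |
|---|---|---|
| No cut-off (t test) | 4.8% | 5.0% |
| Fixed in advance | 5.0% | 4.4% |
| Pooled median | 6.9% | 3.4% |
| Best for a label unrelated to arm | 4.9% | 5.0% |
| Best separation of the arms, 10th–90th percentile | 40–41% | 39% |
| Best separation of the arms, 25th–75th percentile | 28% | – |

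Only the last two rows show real inflation. The median rows fall on either side of 5% because of discreteness.

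**3. Optimism of a cut-off judged on its own data.** Take a label that has no relation to temperature, so that the true Youden index (sensitivity + specificity − 1) is 0. The best apparent index then averages about 0.22 in 60 women and 0.19 in 72 if either direction is allowed. It averages about 0.14–0.15 if the direction is fixed beforehand.

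**The case against.** A reader might infer that the plan sets the cut-off from the trial's own data, replaces the continuous outcome with a category, compares the arms on it, and so inflates false positives. The document states none of these steps.

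- The source of the cut-off is not given. That it will be data-derived is the natural reading, but it remains an inference.
- The sentence first defines a continuous variable. The section also provides a t or Wilcoxon test, a standardised effect size for means, and linear regression. The continuous comparison is therefore already open under the plan.
- The Outcomes section links temperature patterns to stage, which suggests a descriptive use of the cut-off.
- Inflation to 28–40% requires a search on the arm contrast, which nobody proposes. A cut-off chosen for another purpose keeps the error near 5%.
- The statistician is blinded. This makes it less likely that a known arm is favoured, although a search between coded groups remains possible, and blinding does nothing about power or optimism.
- An article may leave the value and derivation of a secondary cut-off to the full protocol or analysis plan.

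Most of this stands, and it makes the consequences conditional. It does not remove the point. The article itself commits to a cut-off as part of the analysis of a continuous outcome, offers two test routes, and gives neither priority. That is a loosely fixed analysis choice and not only an absent detail.

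**Conclusion.** The concern holds in conditional form. The plan introduces a thermography cut-off without a value, source or rule, and leaves open which form of the outcome carries the arm comparison.

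- If the category is compared between arms, roughly 12 points of power are lost with a median split at 30 per arm (about 80% to 68%). Other cut-offs cost 18 to 25 points (79% to 61% or 54%).
- If the cut-off is also chosen on the arm contrast, type I error can reach about 28–40%.
- If it is chosen without regard to arm, there is no systematic inflation, but accuracy read off the same data is over-optimistic.

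The power figures rest on normal data, equal SDs and an assumed d; the article supplies nothing from which to estimate d. The document does not support the flat statement that the planned analysis inflates false positives. Thermography is secondary and outside the sample size calculation, so the primary conclusion is not at risk. The change is still worth making, because it removes the ambiguity under every reading of the sentence.

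**What to change.** In Statistical methods {20a}, replace the cut-off clause with three statements:

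1. The variable for the arm comparison is the continuous between-limb temperature difference at day 30, adjusted for its baseline value, analysed separately in phase 1 and phase 2. As a model: day-30 difference = intercept + arm effect + slope × baseline difference. Report the arm effect with its 95% confidence interval.
2. No dichotomised thermography result is used to compare arms.
3. Any cut-off is exploratory and derived without reference to arm. If sensitivity and specificity are given, they are corrected for optimism, for example by bootstrap.

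The wording should be settled before thermography is examined in the 30-day analysis described under Interim analyses {21b}. If that analysis has already been run, the report should say so.

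The cost is wording. The section on assessment and collection of outcomes {18a} already has thermography measured before and after the first 30 days, so no new data are needed. The downside is that the trial cannot claim a validated clinical threshold.

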### Objectives {7}

The primary aim of this study is to evaluate the effectiveness of a self-adjusting compression garment (ReadyWrap®) in reducing and maintaining upper limb volume in women presenting breast cancer-related lymphedema compared to standard compression therapy. Secondary objectives consist in comparing upper limb volume and tissue changes, muscle strength, functionality, and symptoms, as well as health-related quality of life, while also assessing the incidence of adverse events, treatment adherence, and material and professional costs according to the intervention group.

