### Provisions for post-trial care {30}

If an increase of over 10% of the initial volume of the upper limb presenting lymphedema is observed during the 30-day reassessment after participant inclusion, compromising patient functionality and/or quality of life, the participant will be directed to the standard treatment offered by the institution’s physiotherapy service. At the end of the study, regardless of the allocation group and results, participants will be directed to lymphedema treatment according to the institutional routine.

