#### Treatment costs

The following will be considered in the cost analysis: treatment time, number of sessions, material expenses per patient in each treatment phase, transportation expenses to the hospital from home, and food expenses in the hospital. The patient’s expenses will all be considered, including companion expenses, if any.

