## Discussion

This study will evaluate the effectiveness of the self-adjusting garment (ReadyWrap®) in the treatment of lymphedema secondary to breast cancer in Brazilian women compared to the gold standard treatment for volume reduction (phase 1) and maintenance (phase 2) comprising a compressive bandaging and a compressive mesh, respectively. Outcome results will provide data based on both quantitative responses and self-reported participant outcomes. The study will also assess the cost-effectiveness of the ReadyWrap® treatment versus standard care. Finally, after the data analysis, we expect to propose another compression modality for the treatment of this extremely complex and impactful condition.

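### The single rule for continuous outcomes lets a rank test decide the cost comparison, although a cost statement needs the difference in arithmetic mean cost per woman

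*Protocol article*

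**What the plan says.** The section Statistical methods for primary and secondary outcomes {20a} sets out one way to compare groups. It says "Data normality will be calculated using the Kolmogorov–Smirnov test", and that the comparison is then by Student's t "test or Wilcoxon test for continuous variables and chi-square test for categorical variables". It does not say in words that the normality result chooses between the two tests, but no other role for the check is given. The same section adds Glass's delta for mean outcomes and linear regression, and ties neither to costs.

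Costs fall within that section's scope. The Objectives {7} list "treatment adherence, and material and professional costs according to the intervention group" among the secondary aims. Treatment costs, under Secondary outcomes, is built per patient from "treatment time, number of sessions, material expenses per patient in each treatment phase, transportation expenses to the hospital from home", together with food and companion expenses. The Discussion makes an economic promise: "The study will also assess the cost-effectiveness of the" garment against standard care, and the Abstract says the same. Nowhere are costs given a different method.

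**The concern.** A cost comparison informs a budget, and only the arithmetic mean multiplied by the number of women treated gives a budget. The Wilcoxon test asks whether a woman in one arm tends to cost less than a woman in the other. It takes no account of how expensive the costly minority is. Cost data are often right-skewed, so a normality check is likely to send them to the rank test. The question answered would then move from mean cost to rank order without anyone having decided that it should.

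The economic message of the trial is at stake: a reported saving, or a reported extra cost, that the mean cost per woman does not support. The primary outcome is not affected.

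**Working it through.** **Inputs from the document.** Group size is 36, from Sample size {14}. To reproduce it: for 45% against 80%, two-sided 5%, 80% power and pooled variance, n = [1.96·√(2 × 0.625 × 0.375) + 0.84·√(0.45 × 0.55 + 0.80 × 0.20)]² / 0.35² = (1.342 + 0.537)² / 0.1225 ≈ 28.8, so 29. The plan's 30 gives 81.6% power, and 30 × 1.2 = 36. This only fixes n; the document states no figure for costs.

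**Assumed inputs.** Control cost is Normal with mean 100 and a given SD. ReadyWrap cost has the same SD around 80 for 5/6 of women and around 200 for 1/6. The true means are equal: 5/6 × 80 + 1/6 × 200 = 66.7 + 33.3 = 100.

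**Why the rank test moves.** Wilcoxon responds to P(ReadyWrap woman costs less than control woman), which is 0.5 under its null. Here it is 5/6·Φ(20/(SD√2)) + 1/6·Φ(−100/(SD√2)):
- SD 10: 5/6 × 0.921 + 0 = 0.77
- SD 20: 5/6 × 0.760 + 0 = 0.63
- SD 30: 5/6 × 0.681 + 1/6 × 0.009 = 0.57

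Moving the costly group from 200 to 240 raises the ReadyWrap mean to 66.7 + 40 = 106.7 but leaves these probabilities almost unchanged.

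**Simulation.** 36 per arm, two-sided 5%. The rule is Lilliefors-corrected Kolmogorov–Smirnov in each arm, then Wilcoxon if either arm is non-normal, otherwise Student's t. True means are equal in every row. The entries are the share of trials declaring ReadyWrap cheaper; ranges are over repeated runs of about 2,000 trials each.

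| ReadyWrap cost pattern | SD 10 | SD 20 | SD 30 |
|---|---|---|---|
| 80, with 1/6 at 200 | 98% | 47–51% | 14% |
| 83.3, with 1/6 at 183.3 | 93–94% | 29–33% | 7–10% |
| 91.7, with 1/12 at 191.7 | 65–67% | 12–13% | 5% |
| 90, with 1/6 at 150 | not run | 6% | not run |

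In the first three rows Welch's t declares ReadyWrap cheaper in about 3% to 7%; the nominal figure in one direction is 2.5%. With an uncorrected Kolmogorov–Smirnov test the first row at SD 20 falls to 36%.

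**Other shapes.**
- Lognormal costs with equal means, log-SD 1.0 in the ReadyWrap arm against 0.3 in control: rule 68%, Welch 9%.
- Same shape in both arms: 1% to 3%, which is nominal.
- Heavier tail in the control arm: close to 0% declare ReadyWrap cheaper. By symmetry of the two arms, the inflated error then declares it dearer.

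**The case against.** The strongest reply is that the statistical section never mentions costs, that the normality check is not expressly said to choose the test, and that cost-effectiveness cannot come from a two-sample test at all. Health-economic methods may sit in a fuller protocol or economic plan that a journal article leaves out. This carries some weight. But the point does not rest on a missing economic plan. The published rule is headed for primary and secondary outcomes, costs are one of those outcomes, and the rule as written is unsuitable for them.

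A reader might go further and infer that the plan will produce a false saving for ReadyWrap, because women who stop the garment are sent to standard treatment and carry both costs, at the rate of 6 in 36 implied by the sample-size allowance. The documents do not support that:
- The 20% allowance covers losses to follow-up and interruptions together, in every group. A woman lost to follow-up does not incur double costs.
- Suspension under {11b} applies to both arms. Under Provisions for post-trial care {30}, "the participant will be directed to the standard treatment offered by the" physiotherapy service only after a specified volume increase that compromises function or quality of life, again in either arm.
- No passage puts care after a switch into the cost outcome.
- If ReadyWrap cost 80 and standard care 100, carrying both would be 180, not 200. The ReadyWrap mean would then be 5/6 × 80 + 1/6 × 180 = 96.7, a real saving. The 83.3/183.3 row keeps costs additive with equal means, and its results are smaller.
- In phase 1 the control arm attends twice a week, so travel and companion costs could make control the more skewed arm. In phase 2 the visit schedules match.

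Glass's delta and regression are based on means and might expose a contradiction, but neither is assigned to costs.

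**Conclusion.** The point holds in a limited form. The stated rule covers costs, by implication leads to a rank test when they are skewed, and so need not compare mean cost per woman. Where the arms differ in shape it can indicate a cost difference absent from the means, for or against ReadyWrap. Where the shapes agree it does no harm.

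The size cannot be known from the documents. The range of about 10% to 98%, and about 5% at the weakest tail tried, rests entirely on an assumed costly minority in one arm and an assumed spread. It shows that the error can be large, not that it will be. Neither its direction nor a false saving for ReadyWrap can be predicted. The point concerns one secondary outcome: a cheap improvement, of low to moderate severity.

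**What to change.** Add a sentence to the statistical methods: costs are exempt from the normality rule; in each phase, the arithmetic mean cost per randomised woman is compared between arms with a 95% confidence interval from a non-parametric bootstrap (or Welch's t), whatever the Kolmogorov–Smirnov result. A bootstrap interval is the natural first choice, since Welch itself exceeded its nominal level under the heaviest skew tried.

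State also that the cost of lymphedema care received after a switch during follow-up counts in the arm to which the woman was randomised. This follows the intention-to-treat statement in {20c} and keeps the costly tail in the comparison.

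The price is one or two sentences, a bootstrap run, and an interval that may be wider than a rank-test p-value would suggest. No extra participants are needed.

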### Interim analyses {21b}

An initial analysis is planned with the data obtained in the 30-day evaluation after study inclusion of each volunteer for both groups, with the statistical analysis carried out by the blind researcher according to the statistical planning.

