### Methods in analysis to handle protocol non-adherence and any statistical methods to handle missing data {20c}

Outcome assessments will be performed by intention to treat and protocol adherence will be verified.

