### Composition of the data monitoring committee, its role and reporting structure {21a}

A data monitoring committee was not formed for this study. This decision was made based on the absence of serious adverse effects by the applied treatments, both in the experimental treatment and the control, which is the institution’s standard. In any case, control and notifications by the research physiotherapists involved in the study of possible adverse effects and undesirable symptoms reported by the volunteers will be performed. If unwanted effects resulting from the treatment are observed, the participant will withdraw from the study and the institutional routine will be conducted, depending on the situation, and all necessary medical support will be provided.

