### Adverse event reporting and harms {22}

The occurrence and intensity of the following symptoms will be verified during the first and second treatment phases through reports and notes made in the therapeutic diary: contact dermatitis, skin infection, uncompensated arterial hypertension, and worsening of upper limb volume by 10% of the initial volume, among other unforeseen effects. In addition, all participants will also be provided with a telephone contact that will serve as a communication channel between participants and therapists for reporting adverse events, unpleasant symptoms, questions about lymphedema treatment, and guidance, when relevant. Treatment suspension before the proposed period will take place when side effects are observed, such as allergic reaction or poor adaptation to the applied material, increase in upper limb volume by 10% of the initial volume, affected upper limb infection, and decompensated blood pressure. If any other unforeseen change occurs, the case will be evaluated by the health team and the necessary procedures will be adopted.

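### The 6- and 12-month comparisons of continuous outcomes, as written, make no use of the 30-day values of women who later leave, and can be biased if leaving depends on early response

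*Protocol article*

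**What the plan says.** - **Schedule.** Under Plans for assessment and collection of outcomes {18a}, perimetry, thermography and dynamometry are "performed before and after the initial 30 days of treatment and during follow-up (6 and 12 months". Each woman can therefore give three post-baseline values per outcome.
- **Tests.** Statistical methods {20a} compares groups by Student's t "test or Wilcoxon test for continuous variables and chi-square test for categorical variables". The only modelling named is regression: "Associations between the variables of interest and the outcome will be performed using univariate linear regression", followed by a stepwise multiple linear model. No visit term, subject effect or repeated-measures model appears.
- **30-day data.** Interim analyses {21b} gives these their own analysis: "An initial analysis is planned with the data obtained in the 30-day evaluation after study inclusion of each volunteer for both groups".
- **Losses.** Sample size {14} expects them: "To cover possible losses to follow-up and treatment interruption, a total of 20% will be added to the number of participants".
- **Analysis principle.** Section {20c} says "Outcome assessments will be performed by intention to treat and protocol adherence will be verified" and names no method for missing values.
- **Leaving the study.** Section {21a}, on the data monitoring committee, says "If unwanted effects resulting from the treatment are observed, the participant will withdraw from the study". Section {22} lists "worsening of upper limb volume by 10% of the initial volume" among the harms to be recorded.

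**The concern.** A two-sample test takes one value per woman. Applied at 6 or 12 months, it keeps those measured at that visit and drops the rest, although the 30-day values of the dropped women are already in the database. If the women who leave are mainly those who responded poorly at 30 days, the completers are a selected group. If the selection differs between arms, part of the late difference comes from who stayed.

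The protocol makes response-related loss plausible: {21a} takes women with unwanted treatment effects out of the study, and {22} counts volume worsening among those effects. At stake is the late-outcome comparison, for which the 12-month follow-up is planned and which the Discussion lists as a strength.

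**Working it through.** **The plan's own figure.** For 45% versus 80%, two-sided 5% and 80% power, the pooled-variance formula gives 29 per group against the stated 30. Then 30 × 1.2 = 36 per group, and 4 × 36 = 144, as stated. These numbers are not in dispute. The six added per group are 6/36, or 1 in 6 of those enrolled.

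**Inputs from the protocol:** 36 per arm; loss of 1 in 6, with 20% as the upper case; 5% significance level.

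**Assumptions, not in the protocol:** 30-day and 12-month values are bivariate normal in SD units (higher is better), with correlation ρ of 0.5 to 0.7. All loss occurs after day 30. Where loss depends on response, its log-odds fall by 1.5 per SD of better 30-day response.

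**Formula.** Let m be the amount by which the mean 30-day value of women who stay exceeds that of all women in the arm. The completers' 12-month mean is then shifted by ρ × m, and the bias of the contrast is ρ × (m in experimental − m in control).

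**(a) Loss follows response in one arm only; no true effect.** Integrating the loss model over the normal distribution gives m = 0.192 at 1 in 6 lost and 0.227 at 20% lost. The other arm loses the same share at random (m = 0). With n women left per arm, SE ≈ √(2/n). With k = bias/SE, type I error = Φ(−1.96 + k) + Φ(−1.96 − k).

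| Loss | n left per arm | SE | ρ | Bias (SD) | k | Type I error |
|---|---|---|---|---|---|---|
| 1 in 6 | 30 | 0.258 | 0.5 | 0.096 | 0.37 | 6.6% |
| 1 in 6 | 30 | 0.258 | 0.7 | 0.135 | 0.52 | 8.2% |
| 20% | 28.8 | 0.264 | 0.5 | 0.113 | 0.43 | 7.1% |
| 20% | 28.8 | 0.264 | 0.7 | 0.159 | 0.60 | 9.2% |

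Simulation with 36 per arm agrees: bias 0.10 to 0.16 SD, type I error about 6 to 10%. If the SD of percent volume change were 8 to 10 points (assumed), that is 0.10 × 8 = 0.8 to 0.16 × 10 = 1.6 points. The bias favours whichever arm loses its poor responders.

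**(b) Same response-driven rule in both arms.** With no true effect, m is equal in the two arms, so the bias is 0; simulated type I error is 4.5 to 5.5%. With a true effect of 0.5 SD, the worse arm loses more women:
- 1 in 6 lost overall: m = 0.233 in control and 0.151 in experimental. Bias = ρ × (−0.082) = −0.041 to −0.057 SD.
- 20% lost overall: m = 0.272 and 0.181. Bias = ρ × (−0.091) = −0.046 to −0.064 SD.

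Simulation gives 0.03 to 0.06 SD, always toward no difference.

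**(c) Loss unrelated to response.** m = 0 in both arms, so there is no bias. Using the 30-day values reduces the standard error by only about 2 to 4%.

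**Likelihood comparison.** An estimate that uses every woman's 30-day value adds the ρ × m shift back. In a large-sample run (one million per arm, 20% lost) it was within 0.003 SD of the true difference in all three patterns.

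**The case against.** **The discarding is inferred.** {20a} names tests; it does not say that they are confined to women present at the visit. {20c} states intention to treat, and a t test could follow imputation set out in an analysis plan that is not shown. This stands in part, and the missing imputation method is not itself the point. The point is the stated method: the tests and regressions named do not use earlier values of women without a late value.

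**Type I error need not exceed 5%.** A reader might infer general inflation. The documents do not support that. The rules on suspension, redirection and withdrawal apply alike to both arms, and with a shared rule and no effect there is neither bias nor inflation. With an effect, the shared rule makes a superiority comparison conservative. Arm-specific loss is possible because the devices differ and allocation is known, but it is an assumption.

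**Not every volume rise means leaving.** A reader might also treat {11b} and {30} as rules that end follow-up. {11b} suspends treatment. {30} directs a woman to standard treatment, and only if function or quality of life is also compromised. Neither stops assessment by itself; only {21a} speaks of leaving the study. The volume rule alone may also remove few women. In phase 1, with an assumed mean change of −10% and SD of 8 to 10, a rise above 10% lies 2.5 to 2.0 SD out, or 0.6 to 2.3% of women. In phase 2, with an assumed mean of 0, it is about 11 to 16%.

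**A mixed model does not by itself restore intention to treat.** It predicts the late values of women who left from those of women who stayed. That stands, and it shapes the fix.

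**Conclusion.** The concern holds in conditional form, for the 6- and 12-month contrasts of continuous outcomes only. The separately planned 30-day analysis is untouched, and so is the chi-square responder comparison on which the sample size rests.

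The size depends on how women leave: about 0.10 to 0.16 SD with type I error of about 6 to 10% under one-arm response-driven loss; about 0.03 to 0.06 SD toward no difference under a shared rule at a true effect of 0.5 SD; and nothing under a shared rule with no effect or under random loss. The correlation, the strength of the dependence and the placing of all loss after day 30 are assumptions. The protocol makes response-related loss plausible but does not show that it differs by arm. Nor does it establish that the late comparison fails intention to treat in every case; that turns on whether women who stop treatment are still measured. The change is worth making because it guards against a plausible bias at little cost.

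**What to change.** In {20a}, for each phase and each continuous outcome, make the main analysis of the late visits a linear mixed model for repeated measures:
- Terms: arm, visit (30 days, 6 months, 12 months) and arm-by-visit, with unstructured covariance.
- Population: all randomised women with any post-baseline value.
- Report: the arm difference with 95% CI at each visit.
- Keep the t and Wilcoxon tests at single visits as sensitivity analyses.
- Include the 6- and 12-month measurements of women who stopped or changed treatment but were still assessed. Reconcile the wording of {11b}, {30} and {21a} so that it is clear who remains under assessment.

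**Cost.** Wording in the statistical section only; no new data, visits or patients. SPSS, the named software, fits the model through its MIXED procedure.

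**Downside.** The model assumes that missingness is explained by the observed values. Add a sensitivity analysis for departures from that assumption. Randomised women with no post-baseline value remain outside the model, so report their number by arm.
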